**Environmental**						
NEWS-A [92, 93]	Neighborhood walkability	x				
Social Support for Healthy Behaviors [94]	Perceived social support for healthy eating and PA	x	x	x	x	x

*BARSE* Barriers Self-Efficacy Scale, *BREQ-3* Behavioral Regulations for Exercise Questionnaire version 3, *BRFSS* Behavioral Risk Factor Surveillance System, *DFAQ-CU* Daily Sessions, Frequency, Age of onset and Quantity of Cannabis Use inventory, *EARLY* Early Adult Reduction of weight through LifestYle intervention trials, *GPAQ* Global Physical Activity Questionnaire, *IPIP* International Personality Item Pool, *NEWS-A* Neighborhood Environment Walkability Scale – Abbreviated, *PA *Physical Activity, *PANAS* Positive and Negative Affect Scale, *PEMS* Palatable Eating Motives Scale, *POMS* Profile of Mood States, *Q* Questionnaire, *RED* Reward-based Eating Drive scale, *TSRQ* Treatment Self-Regulation Questionnaire, *UPPS+P* Urgency Premeditation Perseverance Sensation Seeking + Personality Pathway Questionnaire, *WEL-SF* Weight Efficacy Lifestyle Questionnaire Short-Form

^a^Adapted from a measure published by Brook et al. [79]

^b^Optional

Executive control will be assessed using computerized task-based measures of executive function (i.e., attention, inhibition, working memory, and set-shifting) and impulsivity (monetary 5-trial adjusting delay discounting task [95]) performed at baseline and at weeks 13, 26, 52, and 78. The battery of computerized tasks to assess key domains of executive function will be deployed locally on a secure study computer and iPad coded by participant ID. The Urgency Premeditation Perseverance Sensation Seeking + Personality Pathway (UPPS+P) questionnaire [84] will be administered once at baseline as a measure of impulsivity.

### Participant timeline {13}

See Table 3 for the schedule of enrollment, randomization, interventions, and assessments for study participants.

### Sample size {14}

An a priori power calculation was performed for the primary outcome (weight) using nQuery 7.0 (Statistical Solutions Ltd, Cork, Ireland). In our power analyses, we made the following assumptions: (1) power ≥ 0.90 and above for the primary outcome is ideal; (2) the significance level under the null hypothesis will be set at *α* = 0.05; (3) null hypotheses will be tested against two-directional (that is, two-tailed) alternative hypotheses; (4) a 3-kg between-group difference in weight loss was deemed the minimum difference of clinical importance; and (5) the primary analysis will use the intent-to-treat principle in which all randomized participants are analyzed. We will enroll 150 participants (75 participants per randomized group) to provide 90% power at 5% significance to detect a between-group difference of 3 kg in body weight at 52 weeks. With an attrition rate of as high as 20%, we retain 82% power in a sensitivity (completer’s) analysis. Standard deviation (SD) of weight loss used in this calculation was 5.6 kg and was based on a 52-week interventional study using the Colorado Weigh program conducted at our research center [96]. There are no previous data for us to estimate the effect size for any of the outcomes at 52 weeks. If superiority of IMF to DCR cannot be established, we will perform a non-inferiority test using 2.26-kg weight loss as a non-inferiority margin. In this case, we would have 79% power to establish non-inferiority of IMF as compared to DCR assuming no difference in effect of weight loss between the two groups.

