Trepanowski et al. compared the effects of DCR vs. alternate day fasting (ADF) vs. a no-intervention control on weight loss at 52 weeks among 100 adults with overweight or obesity (age 18–64, BMI 25–40 kg/m^2^, 86% female) [19]. The DCR protocol prescribed consuming 75% of weight maintenance requirements in weeks 0–26 and 100% of weight maintenance requirements in weeks 27–52. The ADF protocol prescribed consuming 25% of baseline energy needs on fast days and 125% of baseline EI on alternating “feast” days during the weight loss phase (weeks 0–26) and then 50% of baseline energy needs on fast day and 150% of baseline energy needs on alternating “feast” days during the weight maintenance phase (weeks 27–52). Mean weight loss was similar for participants in DCR and ADF at week 26 (−6.8% in DCR vs. −6.8% in ADF) and week 52 (−5.3% in DCR vs. −6.0% in ADF) relative to those in the control group. The dropout rate was higher in the ADF group (29% in DCR, 38% in ADF, 26% in control), raising concerns about long-term tolerance of ADF [19]. In addition, during the initial 13 weeks of the study intervention, participants in DCR and ADF were not provided any behavioral weight loss support and were provided all meals, limiting real-world applicability. Furthermore, participants were instructed to not change their PA, which is not consistent with current guidelines for obesity treatment [17]. Finally, this study involved only a 26-week weight loss phase, with participants in the ADF group encouraged to eat 150% of energy requirements on fed days during the weight maintenance phase (weeks 27–52), which may have contributed to the higher attrition.

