Headland et al. compared weight loss at 52 weeks in 332 adults with overweight or obesity (age 18–72, BMI ≥ 27 kg/m^2^, 83% female) across three randomized groups: DCR (4200 kJ/day for women and 5040 KJ/day for men), a 5:2 IMF protocol (prescribing 2100 kJ/day for women and 2520 kJ/day for men on 2 modified fast days per week), or a week-on-week-off energy restriction prescription (alternating between the DCR energy restriction levels for a week followed by a week of habitual diet) [20]. There were no significant between-group differences in weight loss (−6.6 kg in DCR, −5.0 kg in 5:2 IMF, −5.1 kg in week-on-week-off), body composition, glucose, lipids, or attrition at 52 weeks. However, the overall rate of attrition was high (60% in DCR, 49% in 5:2 IMF, and 58% in week-on-week-off), which limits the generalizability and likely impacted the intent-to-treat results. In addition, the behavioral support was minimal, with participants receiving initial advice from a dietitian, but no ongoing individual or group-based support. Finally, while participants were given a PA goal of 10,000 steps per day, between-group differences in PA levels were not reported.

Lastly, Carter et al. compared weight loss among 137 adults with type 2 diabetes mellitus and overweight or obesity (age ≥ 18, BMI ≥ 27 kg/m^2^, 56% female), randomized to either a DCR protocol (1200–1500 kcal/day) or a 5:2 IMF protocol (2100 kJ/day for women and 2500 kJ/day for men on 2 non-consecutive days/week) for 52 weeks. Participants received individualized behavioral support sessions with a dietician biweekly for the first 3 months and every 2–3 months for the remaining 9 months, with no guidance to increase PA. Attrition was similar across groups (29%) and mean weight change at 52 weeks (−5.0 kg in DCR, −6.8 kg in IMF) and 24 months (−3.9 kg in DCR, −3.9 kg in IMF) was similar between groups [21, 22]. However, this weight loss intervention did not meet the obesity treatment guidelines regarding either behavioral support or PA recommendations. Furthermore, adults with type 2 diabetes mellitus typically have a more difficult time losing weight as compared to adults without diabetes [23], which limits the generalizability of results.

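### The 90% superiority and 79% non-inferiority powers assume that every week-52 weight is observed; at the plan's own 20% attrition the primary mixed model has about 83–88%

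*Protocol article*

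**What the plan says.** Sample size {14} of the protocol article lists its assumptions. On the target: "power ≥ 0.90 and above for the primary outcome is ideal". On the test: "null hypotheses will be tested against two-directional (that is, two-tailed) alternative hypotheses". On the effect: "a 3-kg between-group difference in weight loss was deemed the minimum difference of clinical importance". The same list makes the primary analysis intent-to-treat, covering everyone randomized. With 75 per arm and an SD of weight loss of 5.6 kg, the design is said "to provide 90% power at 5% significance to detect a between-group difference of 3 kg in body weight at 52 weeks". The next sentence brings in dropout, for a completers' sensitivity analysis only: "With an attrition rate of as high as 20%, we retain 82% power". The paragraph closes with a fallback non-inferiority test (margin 2.26 kg, 79% power), with no figure under attrition.

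Items 20a and 20c make the primary analysis a linear mixed effects model with group, time and their interaction. That model is also the main way of handling missing values, under MCAR or MAR. Outcomes {12} places the visits at baseline and weeks 13, 26, 39 and 52.

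**The concern.** The paragraph does not say outright that the intent-to-treat analysis keeps 90% power when people drop out. Its layout says so by implication: 90% stands beside intent-to-treat, and the loss from attrition stands beside the completers' analysis. Analysing all randomized participants is not the same as observing all of them. A likelihood-based mixed model uses the earlier weights of someone who leaves, and these carry part of the information about week 52. It cannot supply the rest.

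The primary analysis is therefore credited with a power that it would not have, in nearly every dropout pattern examined below, at the attrition that the plan itself allows for. The same holds for the non-inferiority test, where the reader has no attrition-adjusted figure at all. If superiority is not shown, the result and the fallback test would both be read against powers that presuppose complete follow-up.

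**Working it through.** **Inputs from Sample size {14}:** difference 3 kg, SD 5.6 kg, two-sided α = 0.05, 75 per arm, attrition 20% (75 × 0.80 = 60 per arm), non-inferiority margin 2.26 kg. The non-inferiority α is not stated there. I use one-sided 0.05, which matches the 90% confidence interval in item 20a and reproduces the printed 79%.

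**Step 1. Reproduce the plan's superiority figures.** SE = 5.6 × √(2/n); power ≈ Φ(3/SE − 1.960). The noncentral t value is given alongside.
- n = 75: SE = 0.914; 3/0.914 = 3.281; Φ(1.321) = 90.7%; t-test 90.3%. The plan says 90%.
- n = 74: t-test 89.9%.
- n = 60: SE = 1.022; 3/1.022 = 2.934; Φ(0.974) = 83.5%; t-test 82.9%. The plan says 82%.

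Both figures are reproduced. Losing one week-52 weight per arm already takes the t-test power just under 90%.

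**Step 2. Power of the primary mixed model at 20% attrition.** Work with change from baseline at weeks 13, 26, 39 and 52, and time as categorical. Let S be the 4 × 4 covariance matrix of these changes and w_k the share of participants whose last observed visit is the k-th. The information per arm is I = 75 × Σ w_k S_k⁻¹, where S_k is the block of S for the first k visits and is padded with zeros. The variance V of the week-52 mean is the last diagonal element of I⁻¹. The effective sample size is 5.6²/V, and power is Φ(3/√(2V) − 1.960).

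Assumed, not in the article: dropout is monotone; correlation between changes at adjacent visits is 0.7 to 0.95 and decays with distance (AR(1)); SDs are 3.5, 4.6, 5.2 and 5.6 kg. With categorical time the three earlier SDs cancel out of the week-52 result.

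| Timing of the 20% loss | r = 0.7 | r = 0.8 | r = 0.9 | r = 0.95 |
|---|---|---|---|---|
| All before week 13 | 83.5% | 83.5% | 83.5% | 83.5% |
| One quarter before each visit | 85.2% | 86.1% | 87.4% | 88.2% |
| All after week 39 | 87.1% | 88.1% | 89.4% | 90.0% |

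These are normal-approximation values, to be compared with 90.7% for complete data. The corresponding effective sizes per arm are 60.0 in the first row, 63.0 to 69.0 in the second and 66.5 to 73.2 in the third. An exchangeable correlation of 0.7–0.8 with evenly spread loss gives 86.7–87.5%, inside the same range.

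**Step 3. Non-inferiority.** Power ≈ Φ(2.26/SE − 1.645).
- n = 75: 2.26/0.914 = 2.471; Φ(0.826) = 79.6%; t-test 79.3%. The plan says 79%.
- n = 60: 2.26/1.022 = 2.210; Φ(0.566) = 71.4%; t-test 71.0%.
- Evenly spread loss, effective n 63.0 to 69.0: SE 0.998 to 0.954; Φ(0.619) to Φ(0.725), or about 73–77%.

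**Step 4. A sensitivity scenario only.** One cited 52-week trial lost "29% in DCR, 38% in ADF, 26% in control", and another cited 52-week trial lost 29% in both groups. Apply 29% and 38% to this design:
- No partial data: 75 × 0.71 = 53.25 per arm gives 78.2% (t) or 78.9% (normal); 75 × 0.62 = 46.5 per arm gives 72.4% or 73.3%.
- Evenly spread loss, r = 0.7–0.95: 81.8–86.8% at 29% and 77.7–85.2% at 38%.

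**The case against.** The strongest reply is that the article already prints the downside. Its 82% at 20% attrition lies below the whole range that I obtain for the primary model, so a careful reader has an upper and a lower bound and can place the mixed model between them. The 0.90 target is called ideal, not required. Power stays above 80% at 20% loss. After the trial, how far a 3 kg difference is excluded will be judged from the confidence interval, not from design power. Enrolment is complete, so no design decision turns on this.

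Most of that stands, and it limits the point to what the figures are said to describe. It does not remove it. The 82% is attached to a different analysis, the 90% carries no statement that it needs complete data, and the non-inferiority power has no lower bound in print.

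Two stronger readings are tempting. A reader might infer that the power arithmetic is wrong; Step 1 shows that it is not. A reader might also infer that the 20% ceiling is refuted by the attrition reported in Introduction {6a}, where one trial's description reads "the overall rate of attrition was high (60% in DCR, 49% in 5:2 IMF, and 58% in week-on-week-off". The article does not support that. Objectives {7} says that the long-term results were not available when the study was designed. The Introduction also separates those trials from this one by their weaker or absent behavioral support, and items 11b, 11c and 18b describe ongoing group support, no withdrawal for non-adherence, tracing after missed visits and payment for completed measures. The cited rates are context, not proof of an error.

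**Conclusion.** The point holds as a misattributed power. The 90% belongs to a comparison with 75 observed week-52 weights per arm. At the plan's own 20% attrition, the primary mixed model has about 83% power if dropouts leave before week 13, about 85–88% if losses are evenly spread, and close to 90% only if all losses follow week 39 with a correlation near 0.95. The shortfall is therefore roughly 2 to 7 points in most patterns.

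Only the 83% floor follows from the article's inputs alone. Everything above it depends on assumed correlations, visit SDs and dropout timing, and on treating time as categorical, which item 20a leaves open. The 79% non-inferiority power is likewise a complete-data figure and falls to about 71% at 20% attrition if dropouts contribute nothing.

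This does not show that the trial is too small or that its sample size should have been larger. It shows that two stated powers need their condition written beside them.

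**What to change.** Reword the sample-size paragraph, or state the following wherever the power is next reported:

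- The 90% (superiority) and 79% (non-inferiority) powers assume that all week-52 weights are observed.
- At 20% attrition, the primary mixed model has about 83–88% power for 3 kg. State the assumed correlation, visit SDs and dropout timing, and mark 83% as the value when dropouts give no post-baseline weights.
- At 20% attrition, non-inferiority power is about 71% if dropouts contribute nothing, with the one-sided 0.05 level written out.
- As a labelled sensitivity scenario, give power at 29–38% attrition: about 72–79% with no partial data and about 78–87% with evenly spread dropout. Note that the trials supplying those rates were not available at design.

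The cost is a few sentences and less favourable headline figures. No participants are added, and neither the analysis model nor the data collection changes.

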### Statistical methods

#### Statistical methods for primary and secondary outcomes {20a}

Baseline characteristics will be summarized by treatment groups using descriptive statistics. Normality assumptions will be evaluated, and transformations used (e.g., square root and log) as appropriate. Body weight is the primary outcome variable and others are secondary or exploratory outcomes. Consequently, no adjustment for multiple outcomes will be applied. *P*-values < 0.05 will be considered significant. Any imbalance in baseline characteristics between groups that could potentially be a confounding factor for the outcome will be adjusted for in the statistical model.

The primary analysis will use the “intent-to-treat” principle and all randomized participants will be analyzed. Each continuous outcome will be analyzed using a linear mixed effects model. The fixed effects of the linear mixed effects model will consist of treatment group (IMF or DCR) and time of measurement (i.e., baseline and follow-up time points) and their interaction. Time of measurement will be treated as a continuous or categorical variable, as appropriate. Test of the interaction assesses the difference in post-intervention change from baseline between two groups and is used to quantify the effectiveness of the intervention. The 90% confidence interval for the interaction will be calculated. Incidence of adverse events, protocol modifications, and attrition will be compared between groups using chi square or Fisher’s exact test as appropriate.

To explore the impact of selected biologic, psychosocial, behavioral, and/or environmental variables on the intervention effect, we will initially apply models similar to those being tested in aim 1, with the addition of a potential effect moderator as a covariate and its interaction term (i.e., intervention × moderator × time interaction) in addition to related two-way interaction terms. Among factors with a significant three-level interaction, we will further use post-intervention weight loss as the outcome and multiple linear regression to examine their association with the outcome and its interaction with intervention. Similar multiple logistic regression analysis will also be conducted with the outcome dichotomized as responder and non-responder using clinical criteria.

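### The 79% non-inferiority power holds at one-sided 5% with complete data; at the listed two-tailed 0.05 it is about 69%, and the plan does not say which level decides

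*Protocol article*

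**What the plan says.** Sample size {14} opens with a list of assumptions for the power analyses. Two of them fix the test level: "the significance level under the null hypothesis will be set at *α* = 0.05" and "null hypotheses will be tested against two-directional (that is, two-tailed) alternative hypotheses". The section plans 75 participants per arm and states "Standard deviation (SD) of weight loss used in this calculation was 5.6 kg". It claims 90% power for a 3 kg difference and adds, for a completers' sensitivity analysis, "With an attrition rate of as high as 20%, we retain 82% power".

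The same paragraph then turns to the fallback. If superiority is not shown, "we will perform a non-inferiority test using 2.26-kg weight loss as a non-inferiority margin", and "we would have 79% power to establish non-inferiority of IMF as compared to DCR", assuming equal weight loss in both groups. It gives no separate alpha or sidedness for this test and no power under attrition.

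Statistical methods {20a} treats P-values below 0.05 as significant and says "The 90% confidence interval for the interaction will be calculated". It does not say what that interval is for. Trial design {8} confirms that non-inferiority was considered a priori, for use if superiority cannot be established.

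**The concern.** The superiority and non-inferiority powers stand in one paragraph under one list of assumptions. A reader who applies those assumptions to the non-inferiority test does not get 79%. The paragraph appears to move from a two-sided 5% test to a one-sided 5% test without saying so.

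This matters because non-inferiority may well be the conclusion that the trial reports. The introduction says that none of the three longer trials found a significant difference between the diets. Objectives {7} concedes that the superiority hypothesis runs against those data. If the level is not fixed in advance, the same result can count as success or failure according to which interval is read. The two readings differ twofold in the risk of wrongly declaring non-inferiority.

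**Working it through.** **Inputs, all from Sample size {14}:** SD 5.6 kg; 75 per arm; superiority difference 3 kg; non-inferiority margin 2.26 kg with true difference 0; attrition up to 20%, which leaves 75 × 0.8 = 60 per arm.

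**Formulas.** SE = SD × √(2/n).
- Normal approximation: power = Φ(δ/SE − z), where δ is the 3 kg difference or the 2.26 kg margin. z is 1.960 for two-sided 5% or one-sided 2.5%, and 1.645 for one-sided 5%.
- Exact version: the noncentral t distribution with 2n − 2 degrees of freedom and noncentrality δ/SE.

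**Standard errors.**
- n = 75: 5.6 × √(2/75) = 0.914 kg
- n = 60: 5.6 × √(2/60) = 1.022 kg

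**Step 1: the plan's superiority figures, two-sided 5%.**
- n = 75: 3/0.914 = 3.281; Φ(3.281 − 1.960) = 90.7% (t: 90.3%). Stated: 90%.
- n = 60: 3/1.022 = 2.934; Φ(2.934 − 1.960) = 83.5% (t: 82.9%). Stated: 82%, which is close.

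The superiority figures therefore follow the listed two-tailed 0.05.

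**Step 2: the plan's non-inferiority figure.** With n = 75, 2.26/0.914 = 2.471.
- One-sided 5%: Φ(2.471 − 1.645) = 79.6% (t: 79.3%). Stated: 79%, so it reproduces here.
- One-sided 2.5%, the relevant half of two-tailed 0.05: Φ(2.471 − 1.960) = 69.5% (t: 69.0%). It does not reproduce here.

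**Step 3: completers at 20% attrition.** With n = 60, 2.26/1.022 = 2.210.
- One-sided 5%: Φ(2.210 − 1.645) = 71.4% (t: 71.0%).
- One-sided 2.5%: Φ(2.210 − 1.960) = 59.9% (t: 59.2%).

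| Non-inferiority power (exact t) | 75 per arm | 60 per arm |
|---|---|---|
| One-sided 5% (90% interval) | 79.3% | 71.0% |
| One-sided 2.5% (95% interval) | 69.0% | 59.2% |

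Of the four cells, only the top left matches the stated figure.

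**Step 4: what the choice of interval does to a result.** Take the planned SE at 75 per arm and the normal approximation. Non-inferiority is shown if the observed shortfall of IMF plus the half-width is below 2.26 kg.
- 90% interval: half-width 1.645 × 0.914 = 1.50 kg, so the shortfall must be below 2.26 − 1.50 = 0.76 kg.
- 95% interval: half-width 1.960 × 0.914 = 1.79 kg, so the shortfall must be below 2.26 − 1.79 = 0.47 kg.

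An observed shortfall between about 0.47 and 0.76 kg would pass on one reading and fail on the other.

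**The case against.** The best defence is that the plan holds together once one-sided 5% is read into the fallback. The 79% is then right, alpha is still 0.05, and the 90% interval in {20a} is the one that matches such a test. A test against a single margin is directional by nature, so the two-tailed assumption can be read as describing only superiority. Most of this stands: one-sided 5% was probably intended. However, the list is introduced as covering the power analyses in general, {14} does not exempt the fallback, and {20a} does not connect its interval to the margin. The reader has to supply the link.

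Some stronger conclusions are tempting, but the document does not support them:

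- A reader might infer that 79% is a calculation error. It is not; it is correct at one-sided 5% with complete data.
- A reader might infer that the fallback exceeds the declared error rate, or that 2.5% is required. The document never states 2.5% for non-inferiority, and a one-sided 5% test keeps the false-claim risk at 5%, equal to the declared alpha. One-sided 2.5% is a legitimate preference, not an obligation.
- A reader might infer that attrition was allowed for in the main superiority power and left out for non-inferiority. The 90% headline also uses all 75 per arm; the 82% belongs to a completers' sensitivity analysis. The fair comparison is that superiority has such a companion figure and non-inferiority has none.
- A reader might take 71% or 59% as the power of the primary analysis. Those are completers' figures. The primary mixed model keeps all randomized participants and uses earlier visits.

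**Conclusion.** The point holds as an inconsistency of test level, of moderate severity. The stated 79% does not follow from the assumptions listed above it. Those give about 69%, some 10 percentage points lower. The level that decides the fallback conclusion is left open between one-sided 5% and one-sided 2.5%, because {14} says two-tailed and {20a} plans a 90% interval without giving its purpose.

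The figures rest on the protocol's SD, margin and sample size, a true difference of zero, and a two-sample comparison of change at week 52. With 20% attrition, power for the primary mixed model would lie between the completers' and the complete-data values: between 71% and 79% at one-sided 5%, or between 59% and 69% at one-sided 2.5%. A single figure within those ranges would need correlations between visits and the timing of dropout, which the document does not give.

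**What to change.** Make {14} and {20a} agree before the analysis, in one of two ways:

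- **(a) Keep one-sided 5%.** State this level for non-inferiority and name the 90% interval, compared with 2.26 kg, as the criterion. Limit the two-tailed statement to superiority, and keep 79% labelled as one-sided 5% with complete week-52 data.
- **(b) Use the 95% interval** for both superiority and non-inferiority, and restate the non-inferiority power as about 69% with complete data.

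In either case add the completers' power at 20% attrition, as is done for superiority: about 71% under (a) or about 59% under (b). Do not write in a specific mixed-model power unless its correlation and dropout assumptions are stated with it.

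The cost is a few sentences in the two sections and in any analysis plan, and a less favourable or more qualified power statement. Trial status reports enrolment as complete; no extra participants are asked for.
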